**Level 4: District Hospital**	eCRF+CDSS	SN, MO	Secondary care available for all health conditions and complications Management of medically complex patients with hypertension and diabetes Generate and update eCRF Use CDSS to develop treatment plan and determine need for up- or down-referral

*ANM* Auxiliary nurse midwife, *CDSS* Clinical decision support system, *eCRF* Electronic case record form, *MO* Medical officer (physician), *SN* Staff nurse

The primary implementation partners for the program include the Department of Health and Family Welfare, Government of Punjab (use of IT tools and altered work flow to deliver routine care); TATA Trusts (conduct training of healthcare workers and technical assistance); and Dell Technologies (development of software and IT infrastructure). Monitoring and evaluation activities for I-TREC will be conducted by AIIMS, CCDC, and Emory University. I-TREC will be implemented in Mukandpur block of Shaheed Bhagat Singh Nagar district, Punjab, India, and evaluated through comparison of program indictors with those observed in the neighboring Sujjon block in the same district (See Fig. 1). The program and comparison locations were selected based on consultation with the Punjab Department of Health and Family Welfare.

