#### Pre- and post-program quantitative cross-sectional community surveys

The community-based evaluation component will assess whether the I-TREC program has an impact on blood pressure and blood glucose awareness, treatment seeking, and control among adults in the community. This evaluation component is critical to learning the real-world impact of the I-TREC program on community-level indicators of the care continuum (screening, treatment, control). Data collected in the program and comparison blocks prior to the program will be compared with data collected from these same blocks after the program using identical procedures. This design allows us to assess and address several threats to validity, including lack of temporal order, comparability across the two blocks (leading to potential confounding by population composition) and secular changes unrelated to our program that affect study endpoints (leading to potential confounding by external factors). Given that we will be sampling separate cross-sections of the population in each group and time point, we do not expect inference to be affected by population aging (maturation threats) over the 3-year program period.

At baseline—prior to intervention—we employed a multi-stage cluster sampling design to obtain a representative sample of adults aged 30 years and older in both blocks under study. Within each block, census data were used to select villages proportionate to population size and subsequently we conducted household mapping and listing to generate a sampling frame for households. Households were selected using systematic random sampling, and one adult man and woman from each household were randomly selected using the Kish method to achieve the desired sample size. At endline, this same procedure will be repeated.

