#### Process measures

In the program block, we will examine measures of adoption and implementation of the IT tools, such as completeness of eCRF forms, acceptance (partial and full) and rejection of the CDSS advisories, time stamp of data entry, the initials of the enterer, and average number of new records per day. In both the program and comparison block, data regarding the total number of patients recorded in the out-patient registry at the facility, numbers screened for hypertension and diabetes, numbers receiving medication from the pharmacy, and numbers referred to higher level facilities will be collected through a combination of paper-based registries and routine NPCDCS reports. The I-TREC evaluation team will obtain these facility-level data using abstraction forms without removing any paper records from premises. In addition, the I-TREC evaluation team will periodically conduct random, unannounced visits to directly observe the number of patients seeking care for hypertension and diabetes facilities in both blocks. Additional data on intervention fidelity measures (e.g., use of eCRF during health visit, measurement of blood pressure and blood glucose, provision of the I-TREC print out to the patient) will also be collected through patient exit interviews and the eCRF backend data.

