The coefficient associated with the interaction term, “program group x pre-post indicator,” is the adjusted DiD estimate accounting for heterogeneity in socio-demographic characteristics. The model will be estimated using generalized estimating equations (GEE) to account for clustering of outcomes within the villages (i.e. village is the cluster variable specified for statistical analysis). Sub-group analyses will examine differences by gender and socioeconomic status.

Data points recorded in the I-TREC system will be analyzed by month to examine trends over time and seasonality. We will also evaluate change patient outcomes over time (e.g., mean SBP change). While several of the I-TREC platform indicators are purely descriptive measures of performance (e.g., mean time for data upload), other indicators of healthcare delivery may be compared between I-TREC facilities and comparison group facilities (e.g., patient volume).

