### Current status

Intervention development and pre-testing were completed in August 2019. Healthcare providers in both blocks received training in December 2019, and the I-TREC program was launched in January 2020. Prior to the program launch, pre-program data collection, including facility and patient assessments, qualitative research, and community survey, were completed. Since March 2020, both intervention roll-out and research activities have been impacted by the COVID-19 pandemic. Specifically, government healthcare system resources have been diverted from NCD care to test and treat patients with SARS-COV-2, national and local lockdown measures have forced intermittent closures of lower-tier health facilities and prevented field staff from conducting routine monitoring activities. In addition, patient flow through facilities—when open—has generally declined, possibly due to fear of contracting the virus while seeking healthcare. Nevertheless, as and when healthcare facilities are operational, the intervention components are being implemented by nurses and physicians in the program facilities and program monitoring activities are underway. We expect intermittent disruptions to intervention implementation and monitoring activities to continue until the COVID-19 pandemic has been fully controlled.

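### With one block per arm and two surveys, the village-clustered interval for the DiD leaves out differential block change, so it does not measure uncertainty about a program effect

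*Protocol article*

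**What the plan says.** All references are to the protocol article.

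- **Assignment.** Under Setting and target population, the program goes to Mukandpur block alone, and its indicators are set against a single other block, "with those observed in the neighboring Sujjon block in the same district". The blocks were not randomised: "The program and comparison locations were selected based on consultation with the Punjab Department of Health and Family Welfare". The section on health outcomes among patients adds that every adult resident of the program block counts as exposed, so exposure varies only between the two blocks.
- **Timing.** Data are collected before launch and again after 36 months (Sources of data for evaluation). The community surveys are separate cross-sections.
- **Analysis.** The Statistical analysis plan section takes the group by pre-post interaction as the adjusted DiD. It is estimated by GEE with robust variance, and "village is the cluster variable specified for statistical analysis".
- **Sample size.** The only clustering allowed for is a village-level intraclass correlation of 0.018.
- **Claim about secular change.** The community-survey section says the design lets the team both examine and deal with several threats to validity, among them "secular changes unrelated to our program that affect study endpoints".
- **Limitations.** The Summary expects variation in drugs, diagnostics and clinicians to act similarly on both blocks, and says the shared district hospital must be allowed for. It does not list one block per arm as a limitation.
- **Events since launch.** Current status reports that "national and local lockdown measures have forced intermittent closures of lower-tier health facilities".

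**The concern.** The program term and any change peculiar to one block are the same contrast. If the program block improved more than its neighbour for a reason unrelated to I-TREC, the interaction coefficient would absorb that difference, and nothing in the model could separate the two. Clustering on village captures how much village means vary within a block. It says nothing about how much two untreated blocks would diverge over three years, and adding villages or adults cannot supply that information.

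The p-value therefore tests whether these two blocks changed differently, which is a weaker statement than that I-TREC changed outcomes. The results are meant to inform the national NCD program and other countries, and those readers will take a 95% interval as uncertainty about the program effect. The text encourages this by saying that the design can examine secular change. With a single pre-program survey there is no pre-program trend to examine.

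**Working it through.** **1. Does any between-block variance enter the plan?** Reproduce the stated survey size, starting from the stated 839 adults per block.

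- Village design effect: 1 + (50 − 1) × 0.018 = 1.882.
- 839 × 1.882 = 1,579; divided by 0.90 for 10% refusal = 1,754 per block; times 2 ≈ 3,509, against the stated 3,508.

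The figure reproduces with village clustering alone, so no between-block term was used.

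**2. Can the data supply one?** Two blocks by two periods give 4 block-period means. The model has 4 parameters at that level (intercept, group, period, interaction). Residual degrees of freedom are 4 − 4 = 0, so no block-level standard error can be estimated.

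**3. Village-clustered SE of the DiD in systolic pressure.** Inputs from the sample-size paragraph: SD 18.5 mmHg, 20% with diagnosed hypertension, 35 villages per block. I assume 1,579 respondents per block in each survey round, independent samples in the four cells, and no gain from covariates.

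- With hypertension per cell: 1,579 × 0.20 = 315.8, or 315.8 / 35 = 9.02 per village.
- Design effect: 1 + (9.02 − 1) × 0.018 = 1.144.
- SE = √(4 × 18.5² × 1.144 / 315.8) = 2.23 mmHg; 95% half-width 4.37.
- With 1,754 per block instead: 350.8 per cell, design effect 1.162, SE 2.13, half-width 4.17.

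**4. Adding block-specific change.** Let s be the SD of the change from first to second survey that is specific to a block. The DiD is a difference of two such changes, so its variance rises by 2s². Actual type I error of the nominal 5% test is 2 × [1 − Φ(1.96 × SE / √(SE² + 2s²))]. The values of s are assumed.

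| s (mmHg) | Total SE | Type I error | Half-width needed |
|---|---|---|---|
| 0 | 2.23 | 5% | 4.37 |
| 0.5 | 2.34 | 6% | 4.58 |
| 1 | 2.64 | 10% | 5.17 |
| 2 | 3.60 | 23% | 7.06 |

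The table uses SE 2.23. With SE 2.13 the type I errors at s = 0.5, 1 and 2 are 6%, 10% and 24%.

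**5. Tipping point for an observed DiD of 5 mmHg**, the planned effect. Significance is lost when 2s² > (5/1.96)² − SE².

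- SE 2.23: 6.51 − 4.96 = 1.55, so s = √(1.55/2) = 0.88 mmHg.
- SE 2.13: 6.51 − 4.54 = 1.97, so s = 0.99 mmHg.

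**6. Link to a per-cell SD.** If each of the four block-period means has its own independent deviation with SD τ, the added variance is 4τ², so s = 1.41τ. The first tipping point is then τ = √(1.55/4) = 0.62 mmHg. The two scales must not be mixed.

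**The case against.** The other side has real strength.

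- **Common drift cancels.** A reader might infer that any drift between the surveys is counted as program effect. The DiD formula rules this out: only differential change matters. A comparison block does deal with common secular change.
- **Differential change is not documented.** The blocks are neighbours, share a district hospital and depend on the same state government for drugs and staff. The article reports local closures but does not say that they differed between the blocks. A reader might also suspect differences between survey teams; the text gives no support for that and plans the same procedures at both rounds.
- **Village clustering is right for its own purpose.** It matches the multi-stage sampling and is suitable for sampling error in the contrast of these two blocks.
- **The assumption is half stated.** The article calls the design quasi-experimental and the study observational. It voices an expectation that structural variation will act similarly on both blocks, which is close to parallel trends.
- **Sensitivity analyses often sit in a SAP, which is not shown.** Their absence alone is no fault. The article also makes no significance claim that could be called overstated.

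All of this limits the point without removing it. The statement that the design can examine secular change is in the article, and it describes something that one pre-program survey cannot do. The cluster variable is also fixed there.

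It is also tempting to think that facility data could settle the matter through an interrupted time series. Counts of patients seen, screened, given medication or referred "will be collected through a combination of paper-based registries and routine NPCDCS reports" in both blocks, but the article promises neither monthly counts nor pre-launch months, and these counts hold no blood pressure values. Launch was January 2020 and disruption began in March 2020, so such a series could not separate COVID-19 from the program without assuming equal shocks in both blocks.

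**Conclusion.** The point holds in a limited form. Differential block-by-period change is fully confounded with the group-by-period term and is absent from the village-clustered SE. The interval is sound as a conditional statement about these two blocks, and is too narrow as a statement about a program effect if that variance exceeds zero.

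The size is illustrative. The document anchors no value of s and the data cannot estimate one, so a reader should not infer that type I error is known to be inflated by any given amount. What the arithmetic shows is fragility. With an SE of about 2.2 mmHg, block-specific change with an SD of about 0.9 mmHg is enough to make an observed 5 mmHg DiD non-significant, and an SD of 1 mmHg doubles the nominal 5% error to about 10%. These figures rest on the article's own SD, prevalence and intraclass correlation, and on the sampling assumptions listed in the working.

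**What to change.** The program has been launched in two blocks, so the changes are to wording and analysis.

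1. **Community-survey section.** Say that the two-wave DiD removes secular change common to both blocks, but assumes parallel trends between them and cannot assess that assumption.
2. **Summary.** List one block per arm as a limitation.
3. **Statistical analysis plan section.** State that village-clustered intervals are conditional on these two blocks. Beside each key DiD, report a sensitivity interval with variance equal to the GEE variance plus 2s², over a range of s fixed in advance, and give the s at which significance is lost. Define s as the SD of block-specific change, on the scale of the fitted interaction coefficient (log scale for the log-binomial models).
4. **Facility data.** Where register or NPCDCS counts exist for pre-launch months in both blocks, use them only as a supporting check of pre-program trends in process indicators (screened, medicated, referred). Do not present them as a check on systolic pressure or as a way to separate COVID-19 from the program.

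Items 1 to 3 need no new data and little extra analysis. Item 4 may need some pre-launch register months abstracted. The price is more cautious conclusions.

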### Summary

This is the first study in India evaluating the composite impact of a clinical decision support system integrated with the Government of India eCRF, combined with modified patient flow and enhanced healthcare provider training. It is also an important early effort to systematically evaluate a program for integrated management of hypertension and diabetes at all levels of the public healthcare system, starting from the sub-centre up to the district hospital. Lessons learned may inform optimal approaches to improve healthcare processes and health outcomes within the public sector healthcare system in India.

The I-TREC program and its evaluation have several strengths but also some limitations. Given the primacy of scalability, the role of research staff is limited to program design, training, monitoring and evaluation. Therefore, the context and conditions of implementation are beyond the control of investigators. For example, the availability of drugs, diagnostic investigations, and clinicians are likely to impact the reach, effectiveness, and implementation of I-TREC but rest in the hands of the state government. Nevertheless, we expect variations in these structural elements to affect both the program and comparison blocks similarly. In order to maintain comparability between the program and comparison block, neighboring blocks within the same district were chosen. However, this means that both blocks share the district hospital, which will have to be taken into account during the analysis. While we will be able to obtain patient data in the program block from the eCRF, no comparable source of data is available to use in the comparison block. Moreover, undue monitoring of the comparison block may inadvertently lead to compensation behaviors on the part of clinicians that could undermine our ability to measure performance differences across the two blocks. The community survey, in part, is designed to mitigate these limitations by providing a well-designed comparison of healthcare processes and outcomes as observed in the program and comparison blocks.

This implementation research is intended to provide evidence of workable programs to manage chronic diseases in India and inform the evolving NPCDCS [34]. Given the similarities in the health system and epidemiologic transition between in India and other low- and middle-income countries, this research has additional scope to potentially inform best practices for management of hypertension and diabetes outside of India. In fact, members of our team ([name]) have collaborated with the World Health Organization (WHO)-Southeast Asia Regional Office and the Republic of Maldives for the development of the “mPEN App,” which is a CDSS tool that draws on similar technologies as what is described here to implement the WHO Prevention of Essential NCDs package in primary health care in the Maldives. We envision that the I-TREC program and evaluation will provide opportunities for continued cross-national collaborations and idea exchange to improve hypertension and diabetes care globally.

### Current status

Intervention development and pre-testing were completed in August 2019. Healthcare providers in both blocks received training in December 2019, and the I-TREC program was launched in January 2020. Prior to the program launch, pre-program data collection, including facility and patient assessments, qualitative research, and community survey, were completed. Since March 2020, both intervention roll-out and research activities have been impacted by the COVID-19 pandemic. Specifically, government healthcare system resources have been diverted from NCD care to test and treat patients with SARS-COV-2, national and local lockdown measures have forced intermittent closures of lower-tier health facilities and prevented field staff from conducting routine monitoring activities. In addition, patient flow through facilities—when open—has generally declined, possibly due to fear of contracting the virus while seeking healthcare. Nevertheless, as and when healthcare facilities are operational, the intervention components are being implemented by nurses and physicians in the program facilities and program monitoring activities are underway. We expect intermittent disruptions to intervention implementation and monitoring activities to continue until the COVID-19 pandemic has been fully controlled.

## Data Availability

Data generated from this study will be made available to researchers upon request. Requests may be made to [name] and will be processed through the I-TREC Data Sharing and Publications Committee.

## Abbreviations

ANM: Auxiliary nurse midwives
AIIMS, CCDC: All India Institute of Medical Sciences, New Delhi (AIIMS), the Centre for Chronic Disease Control
CDSS: Clinical decision support system
DiD: Difference-in-difference
eCRF: Electronic case record form
IT: Information technology
I-TREC: Integrated Tracking, Referral, and Electronic Decision Support, and Care Coordination Program
NCD: Non-communicable disease
NHM: National Health Mission
NPCDCS: National Programme for Prevention and Control of Cancer, Diabetes, Cardiovascular Disease, and Stroke
RE-AIM: Reach, Effectiveness, Adoption Implementation, and Maintenance
